## Abstract

**Introduction:**

Long COVID-19 is a distressing, disabling and heterogeneous syndrome often causing severe functional impairment. Predominant symptoms include fatigue, cognitive impairment (‘brain fog’), breathlessness and anxiety or depression. These symptoms are amenable to rehabilitation delivered by skilled healthcare professionals, but COVID-19 has put severe strain on healthcare systems. This study aims to explore whether digitally enabled, remotely supported rehabilitation for people with long COVID-19 can enable healthcare systems to provide high quality care to large numbers of patients within the available resources. Specific objectives are to (1) develop and refine a digital health intervention (DHI) that supports patient assessment, monitoring and remote rehabilitation; (2) develop implementation models that support sustainable deployment at scale; (3) evaluate the impact of the DHI on recovery trajectories and (4) identify and mitigate health inequalities due to the digital divide.

**Methods and analysis:**

Mixed-methods, theoretically informed, single-arm prospective study, combining methods drawn from engineering/computer science with those from biomedicine. There are four work packages (WP), one for each objective. WP1 focuses on identifying user requirements and iteratively developing the intervention to meet them; WP2 combines qualitative data from users with learning from implementation science and normalisation process theory, to promote adoption, scale-up, spread and sustainability of the intervention; WP3 uses quantitative demographic, clinical and resource use data collected by the DHI to determine illness trajectories and how these are affected by use of the DHI; while WP4 focuses on identifying and mitigating health inequalities and overarches the other three WPs.

**Ethics and dissemination:**

Ethical approval obtained from East Midlands – Derby Research Ethics Committee (reference 288199). Our dissemination strategy targets three audiences: (1) Policy makers, Health service managers and clinicians responsible for delivering long COVID-19 services; (2) patients and the public; (3) academics.

**Trial registration number:**

Research Registry number: researchregistry6173.

Strengths and limitations of this studyStrengths include our interdisciplinary approach, which by combining methods common to engineering/computer science, for example, user-centred design and the human computer interaction lifecycle, with those from biomedicine, such as the Medical Research Council Complex Interventions Framework, promotes the likelihood of an intervention which is not only usable and acceptable, but also effective.Strong patient and public involvement input has helped define user requirements, including conceptualisation of long COVID-19 and focusing on function, fatigue and brain fog as well as ensuring the evaluation measures outcomes of interest to patients and clinicians.Intertwining service and research has enabled the rapid development and deployment of an evidence-based intervention, enabling treatment to reach patients rapidly during the pandemic.Our major limitation is the absence of a comparator group for the evaluation of effectiveness; our focus will be on profiling heterogeneity in recovery trajectories and conducting an exploratory mediation analysis to assess which intervention components and measures of app usage/engagement are associated with change in outcomes.

## Background

Since the emergence of the new coronavirus, SARS-CoV-2 in Wuhan, China in December 2019^1^ and the subsequent COVID-19 variants, it has become apparent that while many affected people make a full recovery, others are left with long-term disabling and distressing symptoms,^2^ known as ‘long COVID-19 syndrome’.^3 4^ Prevalence estimates vary, but at least 50% of hospitalised^5 6^ and 10% of non-hospitalised continue to have symptoms 12 weeks after the initial infection.^2 4^ UK government figures suggest that by the end of July 2021, 5.9 million people in the UK had tested positive for COVID-19, of whom just under half a million (492 933) had been admitted to hospital (https://coronavirus.data.gov.uk/), suggesting that over 750 000 people in the UK may experience disabling symptoms persisting more than 12 weeks.

The pathophysiology of long COVID-19 has yet to be elucidated. It appears to be a multisystem disorder, characterised by variability in symptoms and a fluctuating trajectory,^4^ which significantly impairs people’s ability to work, look after their children, or engage with other activities. Despite variability in the nature and severity of reported symptoms, there are some core symptoms experienced by nearly all those with kong COVID-19: fatigue; cognitive impairment (‘brain fog’); breathlessness; anxiety and depression.^2^ These core symptoms are present in numerous other long-term conditions, and treated with well established, non-pharmacological interventions, including physiotherapy, nutritional advice, cognitive behavioural approaches, sleep hygiene and improving self-management skills. These interventions are most often delivered by Allied Health Professionals (AHP), such as physiotherapists, occupational therapists, clinical psychologists and dieticians, specialising in rehabilitation.

Prior to the COVID-19 pandemic, rehabilitation services were at capacity, and their ability to absorb over half a million additional patients requiring help has been further compromised by redeployment of many AHP to supporting acute services. Additionally, many services are system-focussed, so a patient with long COVID-19 who is breathless, fatigued and anxious could be directed to three different clinicians: a respiratory physiotherapist to help with breathing, a neurophysiotherapist or occupational therapist for fatigue, and a clinical psychologist for anxiety, making treatment extremely burdensome.^7^

One effect of the pandemic has been to rapidly accelerate the move toward the use of digital technologies to support healthcare.^8^ Digitally supported rehabilitation, shown to be effective in other disease areas,^9–12^ has the potential to address the challenge of providing timely healthcare to large numbers of individuals with a highly constrained workforce.^13^ Digital health is not without its challenges: despite being shown to be effective in improving health outcomes, relatively few digital health interventions have made it into mainstream healthcare.^14 15^ There are well recognised problems with implementation at scale; many DHI suffer from poor uptake or inadequate ongoing use,^16^ reducing the likelihood of effectiveness. Furthermore, there are concerns around health inequalities and the digital divide, especially as COVID-19 disproportionately affects people from ethnic minority groups, socially deprived backgrounds and older people.^17^ People from these backgrounds are also less likely to have access to digital technology,^18^ so care delivered digitally risks exacerbating health inequalities. However, it has been shown that the digital divide can be overcome by careful design and implementation into routine healthcare.^19^

### Aims and objectives

The aim is to iteratively design, deploy and evaluate a digitally mediated, remote, supported rehabilitation programme for patients affected by COVID-19, which is used effectively, deployed at scale, and does not widen health inequalities.

Specific objectives are to:

Develop and refine a DHI that supports patient monitoring, remote rehabilitation and identifying patients needing further specialist investigation. To include:Clinical pathways aligned with National Institute for Health and Care Excellence guidelines.^20^A clinician-facing digital dashboard which displays data about individuals and selected cohorts.A patient-facing mobile app to provide targeted, tailored rehabilitation according to patient symptoms. The app will collect patient-reported outcome measures (PROMs) and use intelligent algorithms and machine learning to promote engagement and tailor treatment advice under clinician guidance.Determine implementation strategies to promote adoption, scale-up, spread and sustainability with a view to maximising population impact. To include assessing:How best to integrate the DHI into clinical workflows, so it becomes fully normalised for healthcare professionals (HCPs), and patients experience seamless care.The optimal amount of HCP input (time, skill set) required to support patients to engage effectively with the DHI, including those with low digital literacy, while managing large patient workloads safely.Funding and commissioning models to promote long-term sustainability.Assess the population impact of this model of care. To include:Determining the reach (uptake and engagement) of the DHI, as a proportion of eligible patients and how this varies by demographic characteristics.Exploring its impact on patient-reported outcomes and recovery trajectories.Assessing the cost implications to the National Health Service (NHS) of scaling-up and sustaining it.Determine and mitigate the effect of the digital divide on health inequalities.Identify patterns of differential uptake, use and apparent benefits of the DHI for people from ethnic minority or socially disadvantaged backgrounds.Identify and test actions to mitigate any observed differential.

## Methods

### Overall design

This project will combine research methods common to engineering and computer science (focused on developing a product that is safe, stable and meets user requirements) with those familiar to biomedical, behavioural and health service researchers (focused on effectiveness and population impact). Thus, it will follow the Medical Research Council (MRC) Framework for development and evaluation of complex interventions (phases 1, 2 and 4),^21^ user-centred design (UCD) and the ISO 9241 Human-Computer Interaction (HCI) Lifecycle^22^ for intervention developmentEvaluation will use mixed methods, combining qualitative and quantitative data. The work will be divided into four work-packages (WP) across 2 years, with each WP addressing an objective (figure 1).

**Figure 1 F1:**
[figure not shown]
Living With COVID-19 Recovery organisational structure. DHI, digital health intervention; PPI, patient and public involvement; WP, work packages.

### Key principles

All work undertaken will adhere to two key principles: (A) It addresses concurrently the aims of service and research, with the intention that the two should be mutually beneficial. The service priorities are to deliver a safe, effective and cost-effective service at speed in a resource-constrained environment; research requires us to generate new, generalisable knowledge. (B) Interdisciplinary approach with equal representation. The four communities represented in the team include: (1) patients, represented through patient and public involvement (PPI); (2) clinicians caring for patients with long COVID-19, including respiratory specialists, general practitioners and AHP; (3) industry, in the form of a small-medium enterprise specialising in digital health with substantial experience of deployment in the NHS and other healthcare systems; (4) academics. The academic disciplines represented in the team include computer science, HCI, digital health, behavioural science, social science and implementation research, statistics, health economics, health services research and clinical academics.

### Timeline

This is a 2-year project, that started in September 2020, with WP1 mainly focused on the first year of the project to design and optimise the product. WP3 will mainly be focused on the second year. WP2 and 4 will run throughout both years.

### WP1: development and refinement of the Living With COVID-19 Recovery programme

#### Design

Interdisciplinary team applying agile UCD and HCI methods to iteratively determine user requirements, to develop and refine the DHI by testing it against user requirements including optimising effectiveness in achieving desired behavioural changes (figure 2).

**Figure 2 F2:**
[figure not shown]
Iterative cycles of development and refinement for Living With COVID-19 Recovery. DHI, digital health intervention; HCP, healthcare professional; PPI, patient and public involvement.

Inputs include: user requirements; emerging clinical evidence on Long COVID-19; evidence-based treatments; development of personas (an HCI technique involving developing rich, contextualised descriptions of a range of potential users^14^); qualitative user feedback and quantitative usage data. These data sources will be combined in an interative fashion, with six development cycles planned for the first year (figure 2), starting with an existing platform designed for use in other chronic health conditions such as cancer, rhumatoid arthritis and incontinence.

#### Participants

We have identified three main stakeholder groups for user requirements: patients with long COVID-19; HCPs caring for patients with long COVID-19, and health service managers responsible for long COVID-19 services. Initally, patient user requirements have been determined from PPI; recent ethics approval will allow data collection from patients using the Living With COVID-19 Recovery programme (LWCR) programme. HCPs and health service managers wil be identified initially through snowballing from the research team and subsequently from NHS teams using the service.

#### Data collection

We will use qualitative methods in real-time, including online meetings, interviews and focus groups with the three stakeholder groups, recorded with participant consent. Meetings will be driven by both research and service need to provide real-time insight into the needs of patients, health service managers and HCPs, as they adapt to the evolving pandemic, without imposing additional workload. Documents, including meeting agendas and minutes, and follow-up emails, will also be used as data sources.

Quantitative data: see WP3. For ethical reasons we are unable to contact or collect data directly from patients who have declined the LWCR service.

#### Data analysis

Recordings will be stored securely. Relevant sections will be transcribed by a general data protection regulation (GDPR) compliant transcribing company, anonymised and checked for accuracy. Analysis will be done in two stages: first, a rapid, emergent analysis in parallel with data collection, focusing on actionable findings, fed immediately into the development process. Different data sources will be synthesised by the inter-disciplinary development team, through iterative discussions. Subsequent analysis will be in depth and inductive with transcripts coded by experienced qualitative researchers using NVivo, with additional deductive analysis where appropriate, driven by one of our theoretical frameworks or findings from the literature, critiqued in a multidisciplinary data clinic.

Quantitative data will be anonymised. Initial analyses will be descriptive, with subsequent, more complex analyses focusing on usage patterns with a view to maximising uptake and use.

#### Outputs

Evidence-based DHI which is rapidly and fully integrated into routine care pathways of NHS long COVID-19 clinics nationally. The DHI will be routinely updated with new features for the App and Dashboard, such as questionnaires or content, every few months to increase usability, engagement and effectiveness based on participant feedback. Patients and clinicians will be made aware of changes through notifications on the DHI or emails and supported with a helpline.

### WP2: determine implementation strategies to promote adoption, scale-up, spread and sustainability with a view to maximising population impact

#### Design

Mixed-methods, using quantitative data to measure uptake and use at individual and clinic level, and qualitative data to explore and understand barriers and facilitators to implementation. Data collection, analysis and development of implementation strategies will be informed by normalisation process theory (NPT), 15 23 a sociological theory concerned with the work required to implement, embed and integrate (or ‘normalise’) new practices or technologies into routine healthcare.

#### Setting

The LWCR programme will be implemented in community long COVID-19 clinics nationally; these clinics will cover both urban and rural areas. The use of the LWCR programme is free for any NHS long COVID-19 clinic in England until September 2022. We conceptualise implementation as occuring at the macrolevel, mesolevel and microlevel. We define 'macro' as system level change, such as change across multiple local health economies at national or regional level, for example, NHS England (NHSE), Academic Health Science Networks (AHSNs)^24^ or Integrated Care Systems (ICS).^25^ 'Meso' refers to change across a single clinic or local health economy; and 'micro' refers to change at the level of the individual clinician or patient.

#### Participants

Participants for this WP include anyone with responsibility for implementing change in the delivery of care for patients with long COVID-19 at any level. This includes staff working for NHSE or the Department of Health and Social Care (DHSC) with responsibility for policy and practice; commissioners of care; local health service leaders, such as leads or staff working for AHSNs or ICS, clinical and managerial leads working within or across health service Trusts (acute, primary or community care); clinicians responsible for specific clinics and/or delivering front line care to patients with long COVID-19, and patients with long COVID-19 or their carers. Participants also include professionals with particular relevant expertise needed to support the implementation of LWCR, such as understanding of information governance or procurement regulations in the NHS, and members of the research team with responsibility for setting up and delivering the service.

#### Data collection

Data collection and analysis will be shared across WPs. Additional quantitative data collected for WP2 includes numbers of Trusts showing initial interest in deployment who decide against adoption, and demographic data on HCPs registered on the dashboard, including clinical specialty, level of experience, age, gender and ethnicity, collected through a proforma questionnaire completed by each clinic once only.

Additional qualitative data will include email trails and documents published by DHSC, NHSE, AHSNs, ICS or other health service bodies. Clinician feedback on the service will be collected as part of the cycles of iterative development and refinement. This service-related data may be augmented, where necessary, by specific interviews with selected individuals, for example, to obtain deeper insights into an issue raised in a meeting, or to test emerging interpretations of data. Where possible meetings will be recorded, with participant consent. Field notes and minutes will also form part of the dataset.

Data pertaining to individual uptake and use of the LWCR programme will include feedback from clinicians, particularly focusing on how they introduce the service to patients and steps taken to encourage uptake and use, particularly among patients who are less used to digital technology. Opt-in consent will be sought from patients and clinicians to record specific on-boarding consultations. Patients will be invited to participate in interviews with the research team to explore their experience of long COVID-19, the extent to which the service meets their perceived needs, and what could be done to improve the service for others.

#### Data analysis

Analysis of quantitative data is described in WP3. Qualitative data will be analysed in two stages, as described for WP1, with the first stage focusing on actionable findings to promote deployment and the second focusing on transferable learning about implementation of DHI. In this second stage, data will be analysed inductively, with data-driven codes subsequently mapped onto NPT concepts, looking specifically for disconfirming data or data that does not map onto NPT.

#### Outputs

Outputs from WP2 will include:

A fully developed implementation package, detailing the process of successful implementation of a DHI into routine healthcare in a range of healthcare setting (primary, secondary and community care).A sustainable, scalable business model, allowing for ongoing maintenance and development of the product while it is used at scale.Transferable learning about optimising the integration of digital health into routine care, ensuring optimal use by HCPs and patients, including an understanding of how implementation models can mitigate the digital divide.

### WP3: assess the population impact of this model of care

#### Design

Quantitative workpackage. Population impact is defined as reach multiplied by effect.

#### Participants

The target for year 1 will be to recruit 1000 patients registering with the DHI. This will enable us to estimate the overall proportion of patients engaging with the app with a high-level of precision (maximum width of 95% CI is ±3.2%). Similar or increased levels of precision will be achieved when estimating the proportion of those referred who register with the intervention. The sample size in year 2 has not been prespecified and will depend on practical constraints imposed by the scale of the pandemic as the digital intervention is rolled out nationally. Power calculations will be carried out for the year 2 analyses based on the ‘pilot’ data from year 1. This will include power for the proposed quasi-experimental analysis of the effect of the DHI on outcomes at 3-month and 6-month follow-up.

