##### Recovery trajectories

Generalised linear mixed models (GLMMs) and latent class trajectory modelling will be used to examine stability and change in recovery trajectories for the longitudinal PROMs data, and to identify homogeneous clusters of patients with contrasting clinical phenotypes. Time since registration with the programme will initially be included as a linear covariate, but we will explore the functional form of the effect of time to allow for phenomena such as a plateau in symptom recovery or a period of sudden rapid improvement or relapse. Models will include random slopes and intercepts, allowing for individualised differences in severity of baseline symptoms and subsequent trajectories. Fixed effects will include age, gender, ethnicity, IMD and educational attainment.

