### WP4: determine and mitigate the effect of the digital divide on health inequalities

#### Design

This cross-cutting WP will ensure that the work undertaken in the other three WPs is fully sensitive to the needs of those who might be at risk of exclusion, such as minority ethnic groups, socially disadvantaged or older people. It will seek to identify evidence of the digital divide and health inequalities, and work to mitigate these. We will undertake a systematic scoping review to identify features of DHI design and deployment that enable engagement by people with low digital/health literacy, for example, key content is presented using graphics, video, and audio to enhance accessibility.

In relation to WP1, the focus will be on ensuring that the personas used in developmental design include minority ethnic, socially disadvantaged and older people, to improve usability and engagement in these groups. We will ensure the content is written for a reading age of entry level 3 (attained by over 80% of the UK population)^37^ and therefore, understandable by most patients. Design features will allow family or carers to log in and support patients. The systematic scoping review will inform intervention design and deployment to maximise engagement by people with low digital/health literacy.

In relation to WP2, the focus will be on identifying and exploring factors in the implementation process that could hinder uptake and increase health inequalities, or conversely, help to mitigate inequalities. For example, translation of key content into different languages, the use of digital champions to help support patients, referral to charities that supply smart phones and advise how to access low-cost data or free Wi-Fi, to help facilitate increased access to all groups.

In relation to WP3, the focus will be on ensuring the analysis of the outcome measures can be compared across different demographic groups so that disparities can be identified, and exploring the factors that can influence differential uptake, use, and impact across the different clinics and demographic groups.

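### The year 1 precision of ±3.2%, stated as a maximum, assumes 1000 independent patients and makes no allowance for clustering by clinic

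*Protocol article*

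**What the plan says.** In the protocol article, WP3, Participants:

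- The size: "The target for year 1 will be to recruit 1000 patients registering with the DHI".
- Its purpose: to "estimate the overall proportion of patients engaging with the app with a high-level of precision", with the bound given as "maximum width of 95% CI is ±3.2" per cent.
- A second claim: "Similar or increased levels of precision will be achieved when estimating the proportion of those referred who register with the intervention".

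No design effect, ICC or number of clinics accompanies these statements. The section adds that year 2 power will be worked out from the year 1 data.

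Elsewhere the article describes a clustered setting:

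- WP2, Setting: "The LWCR programme will be implemented in community long COVID-19 clinics nationally".
- WP2, Design: quantitative data will be used to "measure uptake and use at individual and clinic level".
- WP2, Data collection: how clinicians present the service and encourage its use is itself to be studied.
- WP4, Design: WP3 will look at influences on "differential uptake, use, and impact across the different clinics and demographic groups".

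On modelling, WP3, Recovery trajectories, says: "Models will include random slopes and intercepts, allowing for individualised differences in severity of baseline symptoms and subsequent trajectories". The fixed effects it lists are five patient-level covariates. Neither that section nor Usage and engagement, Mediation analysis or Equality names a clinic term.

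**The concern.** Patients of the same clinic share the same staff, the same introduction to the app and the same encouragement to use it. If engagement differs between clinics, 1000 patients carry less information about the overall proportion than 1000 independent ones. A plan that makes clinic differences a research question should not set them to zero when it states the widest interval to expect.

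This precision is the only stated reason for the year 1 size. Year 1 data also feed the year 2 power calculation. If clinic is ignored there too, year 2 power will be overstated.

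**Working it through.** **Inputs from the protocol.** n = 1000 and a 95% interval (WP3, Participants). No expected proportion is given, so the maximum is read as p = 0.5.

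**Reproducing the stated figure under independence.**

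- Wald: 1.96 × √(0.25/1000) = 3.10%.
- Exact (Clopper-Pearson) for 500/1000: 46.85% to 53.15%, half-width 3.15%.
- With z taken as 2: 2 × √(0.25/1000) = 3.16%.

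The stated 3.2% is the independent-sampling value; which variant was used cannot be told.

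**Room left for clustering.** Relative to Wald, (3.2/3.10)² ≈ 1.07 (1.066 unrounded). Relative to the exact value, (3.2/3.145)² ≈ 1.035. With design effect DE = 1 + (m − 1) × ICC for m patients per clinic, the more generous 1.066 allows an ICC of at most:

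- 0.066/19 ≈ 0.0035 at 20 per clinic;
- 0.066/49 ≈ 0.0014 at 50 per clinic;
- 0.066/99 ≈ 0.0007 at 100 per clinic.

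**Half-width with clustering.** Formula: 3.10% × √DE. ICCs and clinic numbers are assumptions, with equal clinics and 1000 patients in total.

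| Assumed layout | ICC 0.01 | ICC 0.02 | ICC 0.05 |
|---|---|---|---|
| 50 clinics of 20 | DE 1.19, ±3.38% | DE 1.38, ±3.64% | DE 1.95, ±4.33% |
| 20 clinics of 50 | DE 1.49, ±3.78% | DE 1.98, ±4.36% | DE 3.45, ±5.76% |
| 10 clinics of 100 | DE 1.99, ±4.37% | DE 2.98, ±5.35% | DE 5.95, ±7.56% |

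Every cell exceeds 3.2%. For 20 clinics at ICC 0.05, the effective sample size is 1000/3.45 ≈ 290. An interval computed as if patients were independent would then cover about 2Φ(1.96/√3.45) − 1 = 2Φ(1.055) − 1 ≈ 71%. Unequal clinic sizes widen this further: with an assumed coefficient of variation of 0.65, DE = 1 + (1.4225 × 50 − 1) × 0.05 = 4.51, giving ±6.6%.

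**The proportion of those referred who register.** Its denominator is at least as large as the number registering, so under independence the claim of similar or better precision follows. With clustering, extra referrals from the same k clinics help less. As m grows, the half-width at p = 0.5 falls only to 1.96 × √(0.25 × ICC/k). For k = 20 and ICC 0.05 that floor is 1.96 × √(0.25 × 0.05/20) = 4.9%.

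**The case against.** The best defence has four parts.

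1. *Maximum* refers to the unknown proportion, and 3.2% is correct in that sense. This stands as a reading of the arithmetic. It does not make the figure a bound once patients within a clinic are correlated.

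2. Clinics are not randomly sampled: any NHS long COVID-19 clinic in England may use the programme. If the participating clinics are taken as fixed and are the whole target, binomial variance is not too small. This stands, and limits the point to inference beyond those clinics. But Key principles aims at generalisable knowledge, WP3, Design, is about population impact, and WP3, Participants, looks to national roll-out, so that wider inference is intended.

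3. The documents give no ICC or clinic number, so the size of the shortfall is assumed throughout. This stands. No decision rule depends on 3.2% either.

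4. An article condenses, and a fuller plan may handle clinic in the models. This stands for the models. It does not help the published precision figure, which an unseen plan cannot change.

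A reader might go further and infer that the mixed models have patient-level random effects only, so that all reported intervals will be too narrow. The documents do not support that. The article says what the models will include, not what they exclude, and WP4, Design, commits WP3 to looking across clinics. Nor do the documents say that deprivation or ethnicity varies mainly between clinics; both are recorded per patient. Contrasts that lie mostly within clinics may be little affected by leaving clinic out.

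**Conclusion.** The point holds for the stated precision. ±3.2% is an independent-sampling figure presented as a maximum in a study that recruits through clinics and plans to examine differences between them. For inference beyond the participating clinics it is too narrow unless the ICC is close to zero (below about 0.0035 at 20 patients per clinic and about 0.0014 at 50).

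The size rests wholly on assumed ICCs, clinic numbers and equal clinic sizes. Over ICCs of 0.02 to 0.05, a layout of 50 clinics gives a modest excess over the stated figure, while 20 clinics give up to nearly twice it (5.8/3.2 ≈ 1.8).

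The modelling point is secondary: the analysis sections name no clinic term, and the article should say how clinic is handled. It matters most for overall means and slopes and for exposures set by clinicians, such as their messaging and review of assessments under Mediation analysis. It is not shown that every reported interval would be too narrow.

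**What to change.** 1. In WP3, Participants, label ±3.2% as assuming independent patients or drop the word maximum, and add a clustered figure with its assumptions. For example: *Allowing for clustering by clinic with an ICC of 0.02 to 0.05 and equal clinic sizes, the half-width would be about ±4.4% to ±5.8% with 20 clinics of 50, or ±3.6% to ±4.3% with 50 clinics of 20.* Replace the layout with the actual number and sizes of clinics where known, allowing for unequal sizes.
2. Qualify in the same way the claim of similar or better precision for registration among those referred.
3. Report both proportions with clinic-clustered intervals, using a small-sample correction if clinics are few.
4. Estimate clinic ICCs from year 1, for engagement and for the outcomes that year 2 power concerns, and carry them into that calculation with their uncertainty.
5. State how clinic enters the longitudinal and logistic models: a clinic random intercept or cluster-robust standard errors, chiefly for overall means and slopes and for clinician-level exposures.

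The cost is a restated figure, one added model term and wider, less favourable intervals. No extra patients are needed.
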